**TRIAL REGISTRATION**

The RCT will be registered with the Australian and New Zealand Clinical Trials Register (ANZCTR) prior to commencing treatment. The study protocol will also be published.

**DATA STORAGE**

Participant data will be de-identified and collected under ethics approval guidelines. Data will be collected and stored for these studies in methods consistent with the guidelines for human research (NHMRC, 2019). Study 1’s Research Data Management Plan via STASH is included in the Appendix Q. Clinical trial data will be stored for 15 years (NHMRC, 2019) on campus in a locked facility, on OneDrive, and on the UTS-provided eResearch platform.

Recordings of interviews will be stored on an encrypted UTS CloudStor folder and deleted from the original source. At the completion of data analysis, interview data will be transferred to a secure eResearch fileshare via UTS’s servers. This will be able to be accessed by the research team only. During the phase of data analysis, non-identifiable data will be used that excludes information such as names and specific addresses. Once the study is complete, non-identifiable data will be written to a password-protected file.

**ANALYSIS PLAN**

To meet the study’s aim (i.e., to understand if the treatment is efficacious for reducing symptoms of anxiety disorders ), the following analyses will be conducted. The main analyses looking at treatment outcomes from the RCT will be carried out using conservative intention-to-treat principles and using mixed-linear models analyses to handle missing data. Mixed-models are a robust statistical approach for analysing longitudinal clinical trial data and these analyses will employ an appropriate covariance structure and maximum likelihood estimation, which provides unbiased estimates in the case of missing data, under the assumption that data is missing at random. These analyses account for the effect of missing data, thus additional participant recruitment to account for drop-out rates is not warranted. Using this dataset, other appropriate analyses arising from secondary papers will also be conducted. Participants have been informed in the PICF that other secondary data analyses will be conducted on the data that they provide during their participation in the research trial. This may include intersectional moderator analyses of treatment efficacy based on person-level stigma moderators from the minority stress model to inform further treatment adaption needs (Barrera & Castro, 2006; Meyer, 2003). Comparisons between the standard treatment and the LGBTQ-affirmative CBT protocol will be compared using benchmarking analyses (Minami et al., 2008).

To understand the treatment’s efficacy, clinically significant change will be measured using three methods. Diagnostic change will be assessed from pre- to post-treatment and at follow-up using the DIAMOND structured interview. Treatment response will be measured using the reliable change index (RCI) of Jacobson and Truax (1991) to understand which change on the OASIS is not attributable to measurement error, but rather is statistically reliable. Any increase in symptoms by the RCI magnitude of change will be defined as deterioration in this trial. Clinically significant change at post-treatment and to follow-up will be defined as a score below the cut score of 8 on the OASIS (Campbell-Sills et al., 2009).

To meet the study’s aim to quantitatively understand if the treatment is feasible and acceptable for LGBTQ+ participants, proportions will be calculated for participant drop-out, questionnaire completion, recruitment, and treatment fidelity. Treatment fidelity will be calculated by summing for each session the total number of treatment components which were coded as ‘present’, divided by the total applicable number of treatment component items (Borrelli et al., 2005). Results will be benchmarked with previous estimates of CBT in the general population and for the Unified Protocol.

To meet the study’s aim to qualitatively understand if the treatment is feasible and acceptable for LGBTQ+ participants, thematic analysis of the qualitative interviews will be conducted in NVivo12 using framework analysis (Ritchie & Spencer, 1994). Six phases will be followed. Firstly, interview transcripts will be read and re-read to understand the data content. Secondly, each transcript will be coded to capture the meaning of participants’ experience in a condensed way. These will be discussed with the research team to cross-check the codes. Across the interviews, codes will then be collapsed. Fourthly, using a thematic map, codes will be sorted into different themes to provide an overview. Fifthly, themes will be refined by checking their coherence with original codes. Lastly, final themes will be decided and named, with production of the analysis report. Selected quotes around causes for treatment non-effectiveness or treatment effectiveness will be reported, with abbreviation if meaning is not affected, to help contextualise quantitative results of treatment efficacy.

To ensure rigour in the qualitative methodology, the model of trustworthiness proposed by Lincoln and Guba (1985) will be used. Lincoln and Guba recommended that researchers can indicate trustworthy findings by demonstrating their research's credibility, transferability, dependability, and confirmability. Recommendations for embedding these criteria in reflexive thematic analyses were made by Nowell et al. (2017), which include: prolonged data engagement; reflexive journaling (i.e., memos); well-organized storage of data, field notes, memos and related documents; debriefing with peers; for referential adequacy of candidate themes, returning to raw data, and; providing detailed description of the research context and an audit trail. Each of these recommendations was included in this studies’ design.

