**OBJECTIVES, DESIGN, AND HYPOTHESES**

The purpose of this study is to examine the efficacy, feasibility, and acceptability of videoconferencing-delivered CBT for anxiety disorders in LGBTQ+ adults. A CONSORT-R compliant, two-group, randomised control feasibility trial (RCT) will examine the research questions. The hypotheses for this study are below:

1. Videoconferencing-delivered, standard CBT will result in significant reductions in symptoms with a large between-group and within-group effect size at post-treatment and three-month follow-up.
2. Videoconferencing-delivered, LGBTQ-adapted CBT will result in a similar degree of symptom reduction when compared to standard CBT.
3. Videoconferencing-delivered standard CBT and LGBTQ-adapted CBT will be feasible to deliver to LGBTQ+ adults with diagnosed anxiety, as assessed by at least 80% treatment fidelity (Borrelli et al., 2005), at least 80% retention following the waitlist period (Fernandez et al., 2015).
4. Videoconferencing-delivered CBT will be acceptable to LGBTQ+ adults with diagnosed anxiety disorders, as assessed in qualitative semi-structured exit interviews and by at least 70% treatment retention and questionnaire completion at follow-up (Fernandez et al., 2015).

The study’s design has two groups:

**Group 1 (*n* = 26): Immediate treatment group.** Group 1 will immediately receive standard, unadapted CBT delivered via videoconferencing. This treatment will be delivered via Zoom. Participants in Group 1 will receive one 50-minute session per week for eight weeks.

**Group 2 (*n* = 26) Waitlist control group.** Group 2 will commence the treatment after a waitlist period of nine weeks, and will recomplete screening measures and their diagnostic interview. Group 2 will receive a similar CBT treatment delivered via Zoom, but this treatment has been tailored to account for the unique challenges experienced by LGBTQ+ people (Pachankis, 2014). LGBTQ-adapted treatment has been shown to be efficacious in previous trials (Pachankis et al., 2015; Pachankis et al., 2020).

A waitlist control was chosen given no studies have currently investigated standard CBT for internalising disorders in LGBTQ+ individuals. As such this study is designed as a feasibility study, phase 1 clinical trial.

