**PARTICIPANT NUMBERS & POWER**

Using G*Power, it was determined that 52 participants would be needed to detect a large, post-treatment, between-group effect size with alpha set to 0.05 and 80% power (Faul et al., 2007). This is because previous meta-analyses have detected large effect sizes for the effect of CBT on anxiety (Cuijpers et al., 2013). Previous preliminary randomised control trials of CBT for LGBTQ+ adults with both internalising and externalising disorders have recruited samples of similar sizes (Pachankis et al., 2015; Pachankis et al., 2020).

Power was also calculated to detect clinically meaningful changes in participant anxiety disorder diagnosis according to DSM criteria. Using the ClinCalc LLC (2024) sample size calculation tool, the recruitment of 42 participants would be sufficient to detect a post-treatment between-group clinically meaningful change in anxiety disorder diagnosis with 80% power and alpha set to 0.05. This is based on the anticipated incidence of anxiety remission drawn from the metanalysis of Springer et al. (2018), which found that 55.8% of anxiety disorder diagnoses remitted after receiving CBT. For waitlist controls, anxiety disorder symptoms in participants in waitlist control fell below the clinical cut-score 15.4% of the time (Scott et al., 2022). Given CBT has not been examined in trials of LGBTQ+ participants with only internalising disorders (Van Der Pol-Harney & McAloon, 2018), an exact power analysis is unable to be determined and is thus an exploratory estimate. However, 95% confidence intervals will be reported with any effect estimates to determine the intervention's precision.

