**4. Questionnaire Administration (pre-treatment, post-treatment, follow-up)**

All participants will complete the symptom screeners online via REDCAP before starting treatment (pre-treatment), after treatment completion (post-treatment), and three months after treatment (follow-up). These questionnaires will be automatically emailed via REDCAP at the allocated time. It is anticipated that it will take 20 minutes to complete the self-report questionnaires at each time point.

The diagnostic interview (DIAMOND) will be administered at post-treatment and follow-up via phone or videoconferencing (and before commencing treatment for the control group). Participants will be contacted to schedule this appointment, and ideally this appointment will be scheduled in the final treatment session. Only the modules that the participants met criteria for at pre-treatment will be administered.

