- **Recruitment.** Given preliminary power estimates, should at least 52 participants be recruited, then the recruitment methods for CBT delivered via video-conferencing for anxiety disorders will be judged to be feasible. Given power estimates to find clinically meaningful differences in anxiety outcomes, should at least 42 participants be recruited, then the recruitment methods used in this trial may have preliminary feasibility for CBT delivered via video-conferencing for LGBTQ+ adults with anxiety disorders.
- **Questionnaire Completion**. Given power estimates and previous drop out-rates, should sufficient participants complete questionnaires to complete adequately powered analyses, the chosen psychometrics may be suggested to be feasible to be completed via telehealth for LGBTQ+ adults with anxiety and depressive disorders.
- **Treatment Fidelity.** Clinician fidelity to the treatment manuals, as assessed by a supervising clinical psychologist based on treatment manual checklists, will also be assessed. Borrelli et al. (2005) recommended that 80% adherence to treatment guidelines might be assessed as ‘high treatment fidelity’. Supervising clinicians will code fidelity to the treatment manual for 10% of sessions.

All self-report data will be collected via REDCAP. The questionnaire administration schedule is outlined in Table 1 below. Participants in the control group will be re-assessed with the pre-treatment measures and diagnostic interview prior to starting treatment.

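### Pre-to-post change starts at Week 0 for standard CBT but at Week 9 for adapted CBT, which can favour standard CBT in their only comparison; the DIAMOND module rule also loses waitlist remitters

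*Protocol*

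**What the plan says.** Secondary objective 1 (Summary) is to benchmark adapted against standard CBT. Hypothesis 2 (Objectives, Design, and Hypotheses) expects that adapted CBT "will result in a similar degree of symptom reduction when compared to standard CBT". The Analysis Plan gives the method in one sentence: "Comparisons between the standard treatment and the LGBTQ-affirmative CBT protocol will be compared using benchmarking analyses".

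The starting point has to be put together from other sections:

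- Study Procedures, section 4, defines pre-treatment as the assessment that precedes therapy.
- Table 1 places *Pre-* at Week 0 and *Post-* at Week 9 for Group 1. For Group 2 it has *Baseline* at Week 0, *Pre-* at Week 9 and *Post-* at Week 18.
- The text just before Table 1 confirms this: "Participants in the control group will be re-assessed with the pre-treatment measures and diagnostic interview prior to starting treatment".
- Objectives, Design, and Hypotheses: "Group 2 will commence the treatment after a waitlist period of nine weeks". The Summary, the risk section and the Treatment section also speak of eight weeks; these statements must be reconciled.
- Analysis Plan: "Diagnostic change will be assessed from pre- to post-treatment and at follow-up using the DIAMOND structured interview".
- Study Procedures, section 4, on the later DIAMOND interviews: "Only the modules that the participants met criteria for at pre-treatment will be administered".

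Participant Numbers & Power expects 55.8% remission after CBT, and on the waitlist "anxiety disorder symptoms in participants in waitlist control fell below the clinical cut-score 15.4% of the time".

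**The concern.** Group 1's change runs from just after selection, at a DIAMOND severity of at least 4, through nine weeks that contain the therapy. It includes whatever would have happened without therapy in those weeks. Group 2 lives through the same first nine weeks untreated, and any change then is removed before its clock starts. The protocol itself expects some waitlist participants to improve, and describes no handling of that change. If untreated improvement is concentrated soon after entry, two equally effective therapies can show different pre-to-post change, with standard CBT looking better. This is the only planned comparison of the two therapies, and the Background links the study to a larger trial that would compare them directly.

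The module rule is a separate matter of data collection. A diagnostic module that was not given at Week 18 or follow-up cannot be recovered in analysis.

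**Working it through.** **1. The plan's own figures.** A two-sided two-sample t test with d = 0.80, alpha 0.05 and 80% power needs 25.5, so 26 per group (52 in all; power 80.7%). Comparing 55.8% with 15.4%, two-sided without continuity correction, needs 21 per group (42 in all; power 80.3%). Both stated sizes reproduce. Both concern immediate treatment against waitlist; none is given for standard against adapted CBT.

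**2. Change scores (OASIS).** Let both therapies have the same net effect e. Let w1 be the untreated improvement in weeks 0–9 and w2 that in weeks 9–18.

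- Group 1, Week 0 to 9: e + w1.
- Group 2 from its own *Pre-*, Week 9 to 18: e + w2. False gap (Group 1 minus Group 2) = w1 − w2.
- Group 2 from Week 0, Week 0 to 18: e + w1 + w2. False gap = −w2.

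The protocol gives no w on the OASIS. Assume w1 from 0 to 0.5 SD and, for illustration, e = 0.80 SD:

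| Course of untreated change | Group 1 | Group 2 from Week 9 | Gap | Group 2 from Week 0 | Gap |
|---|---|---|---|---|---|
| Stops at Week 9 (w2 = 0) | 0.80 to 1.30 | 0.80 | 0 to 0.5 | 0.80 to 1.30 | 0 |
| Continues at same rate (w2 = w1) | 0.80 to 1.30 | 0.80 to 1.30 | 0 | 0.80 to 1.80 | 0 to −0.5 |

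If 0 ≤ w2 ≤ w1, the own-*Pre-* version favours standard CBT or is neutral, the Week 0 version favours adapted CBT or is neutral, and the true difference lies between them.

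**3. Diagnostic change.** Inputs: 26 per group, 55.8% and 15.4%, with the last standing in for diagnostic remission. Assume both arms end with 55.8% remitted and that early remitters stay remitted.

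- Remitted before Group 2 starts therapy: 0.154 × 26 = 4.0. Remitted at the end: 0.558 × 26 = 14.5.
- Group 1: 55.8%.
- Group 2, new remissions over all 26: (14.5 − 4.0)/26 = 40.4%; gap 15.4 points.
- Group 2, new remissions among the 22 still diagnosed: (14.5 − 4.0)/22 = 47.8%; gap 8.0 points.

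Now let the 22 still diagnosed at Week 9 remit at the full 55.8% (12.3 people). Counted among those 22, the gap is zero. Counted over all 26 it is 55.8 − 47.2 = 8.6 points, which comes only from keeping people in the denominator who had nothing left to remit from. From Week 0, Group 2 would show 15.4 + 47.2 = 62.6%, which is 6.8 points in favour of adapted CBT.

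**4. The module rule against Table 1.** Group 1 has one DIAMOND interview before therapy, at screening, on which everyone qualified. Group 2 has two: screening and *Pre-* (Week 9). If *pre-treatment* means the Table 1 column, someone who no longer meets a module's criteria at Week 9 is not given it at Week 18 or follow-up. No one in Group 1 can lose a module this way. The Week 9 interview must itself take its modules from an earlier interview, so the rule cannot be read in one way throughout. The protocol does not say whether Group 2 must still meet criteria at Week 9.

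**5. Precision.** Take the variance of a pre-post effect size as v = 2(1 − r)/n + d²/(2n), with n = 26, d = 0.80 and an assumed pre-post correlation r of 0.5 to 0.7. The 95% half-width for a difference of two, 1.96√(2v), is 0.62 to 0.52 SD.

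**The case against.** The benchmarking sentence names no baseline, a Week 0 OASIS exists in both groups, and the choice of baseline for an exploratory secondary analysis is often left to an analysis plan. This stands in part. Week 9 for Group 2 is inferred from the definition of pre-treatment and Table 1, not stated for Hypothesis 2. The Analysis Plan does, however, fix diagnostic change as pre- to post-treatment, and the module rule governs data collection, which an analysis plan cannot repair.

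A reader might infer that equal therapies are bound to look different, and on every outcome. The documents do not support that:

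- The gap depends on the course of untreated change and can be zero.
- OASIS below 8 at post-treatment uses no baseline.
- The randomised Week 9 comparison does not depend on Group 2's therapy baseline.
- Regression to the mean on the OASIS is indirect, because selection is on DIAMOND severity.

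A reader might also infer that encouraged outside help inflates Group 1's result. The Treatment section's remarks on other services concern the waitlist group, and help begun there could continue into Group 2's therapy and act in the opposite direction. Nor should the gap be read as a share of d = 0.80, which is a between-group effect.

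On the module rule, *pre-treatment* could mean the screening interview, and the OASIS is collected at post-treatment and follow-up regardless. What goes unrecorded under the literal reading is diagnostic relapse, not all sign of worsening.

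Finally, the protocol claims only preliminary efficacy and defers direct comparison to a larger trial. That limits the consequence but does not remove it.

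**Conclusion.** The point holds as a distortion that can occur, not one that must. On the protocol's definitions, untreated improvement in the first nine weeks can count for standard CBT and not for adapted CBT. The direction is towards standard CBT or nil, provided untreated change is an improvement and does not speed up after Week 9. On change scores it is nil if untreated change is absent or continues at the same rate.

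The 8 to 15 percentage points are an illustration. They rest on identical end states, on early remitters staying remitted and on a cut-score rate standing in for diagnosis. On the OASIS the size is unknown; 0 to 0.5 SD is an assumed range, no larger than the half-width of the comparison at 26 per arm. Hypothesis 2 can therefore support only a descriptive statement.

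The module rule, read literally, leaves diagnostic status after Week 9 unrecorded for about 4 Group 2 participants (at 15.4%) and for none in Group 1.

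**What to change.** 1. **Analysis Plan.** Name the starting assessment in each arm for the Hypothesis 2 benchmarking. Report it twice, with 95% confidence intervals: from each arm's own *Pre-*, and from the common Week 0 baseline (for diagnosis, the screening interview). State that the first favours standard CBT or is neutral, and that the second, which sets 18 weeks against 9, favours adapted CBT or is neutral. Present the comparison as descriptive. Agreement between the two versions should not be made a test of similarity, since the protocol gives no margin and the intervals are wide.
2. **Study Procedures, section 4.** Tie the modules at every later DIAMOND interview, in both groups, to those met at the screening interview. Without this, the Week 0 version of diagnostic change cannot be completed for participants who remit while waiting.

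The cost is protocol wording, one extra analysis of data already scheduled, a few extra DIAMOND modules (about 4 participants) and a less definite statement on Hypothesis 2.

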**REPORTING OF ADVERSE EVENTS**

Regular team meetings are conducted between the team and treatment integrity is monitored by registered psychologists. Participants are monitored regularly throughout treatment during their treatment sessions and via self-report questionnaires, available in Appendix P. The Chief Investigator and Student Investigator have completed the good clinical practice training at UTS.

As this study is not trialling the effects of a pharmaceutical drug or medical equipment but rather the effects of talk therapy, potential adverse events to endanger participant safety are rare and unknown (Duggan et al., 2014). As such, no significant safety issues (SSI) or serious adverse events (SAEs) are expected in this study, but may still occur, and so a log will be kept of all SSIs or SAEs that arise including their potential relatedness to the treatment. In all adverse events, the treating clinician will take steps to ensure the participant’s immediate health and safety using clinical judgment in collaboration with the principal investigator. SAEs in this study are defined as hospitalisation, death, adverse events resulting in permanent harm or disability, or life-threatening or otherwise medically significant risks as assessed by the clinician. When detected, SAEs will be reported to the Health and Medical Research Ethics Committee by the principal investigator within 24 hours along with details of the event and actions taken to mitigate risk from the adverse events log. SSIs will be defined as marked deterioration in symptoms measured by a decrease in self-report questionnaires of a magnitude denoted by the reliable change index (Jacobson & Truax, 1991), clinician clinical judgement, or a combination of both. Once detected, participant risk will be assessed as is standard in clinical practice. Participants whose risk level escalates or whose symptoms markedly deteriorate will be encouraged to contact their health professional team, such as their GP, or emergency services, and refer to their safety plan made at the beginning of treatment.

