***Outcome Measures***

***Primary measures***

The following disorder-specific measure will be completed by participants at pre-treatment, mid-treatment, post-treatment, and 3-month follow up.

- **Overall Anxiety Severity and Impairment Scale (OASIS; Norman et al., 2006):** The OASIS is a five-item self-report measure of the severity, frequency and impairment related to symptoms of anxiety in the past week. Items are rated on a 5-point scale from 0 (*little* or *none*) to 4 (*extreme*). A cut-score of 8 is used to determine anxiety levels consistent with an anxiety diagnosis. Good validity and internal consistency have been demonstrated for OASIS in previous studies (Campbell-Sills et al., 2009; Pachankis et al., 2015; Pachankis et al., 2020)

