***Secondary Measures***

All participants will complete the following secondary self-report outcome measures at pre-treatment, mid-treatment, post-treatment, and three-month follow-up:

- **Overall Depression Severity and Impairment Scale (ODSIS; Bentley, 2014):** The ODSIS is a five-item self-report measure of the severity and impairment of past-week symptoms of depression from 0 (*little* or *none*) to 4 (*extreme*). A score of 5 or above has been used to determine clinical levels of depression (Mira et al., 2019). The ODSIS has been shown to have good validity and internal consistency in previous studies (Mira et al., 2019; Pachankis et al., 2015; Pachankis et al., 2020)
- **Generalised Anxiety Disorder Dimensional Scale (GAD-D) (LeBeau et al., 2012):** The GAD-D is a 10-item measure of generalized anxiety symptoms. Participants rate the past-month frequency with which they have experienced GAD symptoms on a five-point Likert scale ranging from 0 (*Never*) to 4 (*All of the time*). This results in a total score ranging between 0 and 40. The GAD-D has been shown to have acceptable psychometric properties (LeBeau et al. 2012).
- **Social Anxiety Disorder Dimensional Scale (SAD-D)** (Lebeau et al., 2012). The SAD-D is a 10-item self-report measure of social anxiety symptoms. Each item is rated on a five-point Likert scale ranging from zero (“*never*” or “*none*”) to four (“*all the time*” or “*extreme*”). The SAD-D has previously demonstrated good validity and internal consistency in previous samples (Lebeau et al., 2012).
- **Panic Disorder Dimensional Scale (PD-D)** (Lebeau et al., 2012). The PD-D is a 10-item measure of panic disorder symptoms. Items are rated on a five-point scale ranging from 0 to 4. The overall assessment is made by a total score, which is calculated by summing the scores for all ten items. The total scores range from 0 to 40. The PD-D has demonstrated good psychometric properties in previous studies (Lebeau et al., 2012).
- **Agoraphobia Dimensional Scale (AG-D)** (Lebeau et al., 2012). The AG-D is a 10-item scale with each item rated on a 5-point scale from 0 (*Never*) to 4 (*All of the time*). The total score can range from 0 to 40, with higher scores indicating greater severity of agoraphobia. The average total score is calculated by dividing the raw total score by 10, as this is the number of items in the measure.

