- **Specific Phobia Dimensional Scale (SP-D)** (Lebeau et al., 2012). The SP-D is a 10-item measure that assesses the severity of specific phobia in individuals aged 18 and older. Each item asks the individual to rate the severity of specific phobia symptoms during the past 7 days. Each item on the measure is rated on a 5-point scale from 0 (*Never*) to 4 (*All of the time*). The total score can range from 0 to 40. Higher scores indicate greater severity of specific phobia.
- **Separation Anxiety Disorder Dimensional Scale (LeBeau et al., 2012):** The Separation Anxiety Dimensional Scale is a 10-item self-report questionnaire that examines the severity of separation anxiety symptoms in adults. Each item is rated on a five-point scale from 0 (*Never*) to 4 (*All of the time*). Total scores range from 0 - 40. Previous studies have demonstrated sound psychometric properties of the scale (Lebeau et al., 2012)
- **Patient Health Questionnaire 9-Item (PHQ-9) (Kroenke et al., 2001):** The PHQ-9 is a 9-item measure of depressive symptoms. Participants rate how frequently they experienced each symptom in the past two weeks on a four-point Likert scale from zero (*not at all*) to three (*nearly every day*). Scores of 10 or greater indicate clinically significant depression symptoms (Manea et al., 2012). The PHQ-9 has been demonstrated to have good psychometric properties in previous studies (Kroenke et al., 2001; Zuithoff et al., 2010).
- **The Lesbian, Gay, and Bisexual Identity Scale (LGBIS) (Mohr & Kendra, 2011).** The 3-item subscale of the LGBIS measures internalised stigma around one’s identity as a non-heterosexual person on a six-point Likert scale, where 1 is *strongly disagree* and 6 is *strongly agree.* The psychometric properties of the subscale have been demonstrated to be sound and have been used in previous clinical trials (Pachankis et al., 2023).
- **Sexual Orientation Concealment Scale (SOCS)** (Jackson & Mohr, 2016). The SOCS is a six-item measure of concealment of sexual identity. It uses a five-point Likert scale from 0 (*Not at all*) to 5 (All the time). The psychometric properties of the scale are sound with adequate reliability and validity (Jackson & Mohr, 2016).

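### The significant-safety-issue definition measures deterioration by a fall in questionnaire scores, which on the protocol's symptom scales is improvement, and it contradicts the Analysis Plan

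*Protocol*

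**What the plan says.** Protocol, Reporting of Adverse Events: an SSI is "marked deterioration in symptoms measured by a decrease in self-report questionnaires of a magnitude denoted by the reliable change index", "clinician clinical judgement, or a combination of both". The questionnaires are in the plural and none is named. SSIs and serious adverse events go into a log that also records possible relatedness to treatment. Serious adverse events have their own definition and reporting deadline, neither of which uses questionnaire scores.

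Protocol, Analysis Plan: the Jacobson-Truax reliable change index (RCI) is applied to the OASIS to measure treatment response, and then: "Any increase in symptoms by the RCI magnitude of change will be defined as deterioration in this trial". Clinically significant change is "defined as a score below the cut score of 8 on the OASIS".

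Protocol, Study Measures, gives the scoring direction of the main symptom scales:
- OASIS (primary): "A cut-score of 8 is used to determine anxiety levels consistent with an anxiety diagnosis".
- ODSIS: "A score of 5 or above has been used to determine clinical levels of depression".
- PHQ-9: "Scores of 10 or greater indicate clinically significant depression symptoms".
- Agoraphobia scale: "with higher scores indicating greater severity of agoraphobia". The specific phobia scale carries an equivalent statement.
- CGI: 7 is the worst rating for both severity and improvement.

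Protocol, Study Procedures, item 6 (Managing Study Procedure Risks): questionnaire responses are monitored, and worsening or persistently high symptoms lead the team to contact the participant. No numerical threshold is given.

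**The concern.** The protocol uses one index for one construct, deterioration, and gives it two opposite directions. The safety section's direction also conflicts with the scoring of the scales it would be applied to. A protocol can leave the calculation of the RCI to a later document, but here it has already fixed both rules, and they disagree.

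What is at stake is the SSI log. The RCI criterion is the only numerical part of the SSI definition. Someone who completes the log, or builds an alert, from that sentence as written would code the wrong direction. Reliable improvement could then be entered as a safety issue, and reliable worsening would go unrecorded unless a clinician picked it up by judgement.

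**Working it through.** The protocol gives no figure to reproduce. The check is one of direction.

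**Step 1: direction of the scales.** The OASIS has five items scored 0 to 4, so its range is 0 to 20. The cut of 8 marks diagnosis-level anxiety, and falling below it is the good outcome, so higher is worse. The ODSIS, PHQ-9, agoraphobia scale, specific phobia scale and CGI run the same way on the protocol's own statements. For the generalised anxiety, social anxiety, panic and separation anxiety scales, the direction is inferred from symptom items scored 0 to 4. The Client Satisfaction Questionnaire runs the other way, but it measures satisfaction and not symptoms, so it cannot explain the wording.

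**Step 2: the two rules side by side.** Let D be the later score minus the earlier score on one symptom scale, and let c > 0 be the RCI threshold.
- Analysis Plan: deterioration if D ≥ c.
- Reporting of Adverse Events, read literally: deterioration if D ≤ −c.

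No value of D satisfies both. On a given scale and interval, everyone who meets the first rule fails the second, for every positive c.

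**Step 3: two literal readings of the safety sentence.**
- If the decrease is the operative measure, the limb selects reliable improvers.
- If marked deterioration and a decrease are both required on the same scale, the limb selects nobody.

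Under neither reading does it identify worsening.

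**Step 4: illustration on the OASIS.** The threshold is c = 1.96 × SD × √(2 × (1 − r)). The protocol gives neither the SD nor the reliability r, so both are assumptions: SD 3 to 4, r 0.80 to 0.90.
- SD 3, r 0.90: 1.96 × 3 × √0.20 = 2.6 points.
- SD 4, r 0.80: 1.96 × 4 × √0.40 = 5.0 points.

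Across this range, a fall from 12 to 6 (D = −6, now below the cut of 8) meets the questionnaire limb of the SSI definition. A rise from 12 to 18 (D = +6) does not, although it is deterioration under the Analysis Plan. The assumed SD and r affect only the size of c. The reversal follows from Step 2 and does not depend on them.

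**The case against.** The strongest reply is that this is a one-word slip with an obvious intention. The governing term in the sentence is marked deterioration, the text that follows deals with participants whose risk rises or whose symptoms worsen, and the Analysis Plan fixes the direction for the whole trial. Sensible staff would not log a recovered participant as a safety issue. That is probably true. But a plain intention does not correct an operative definition, and a log or alert is built from what is written.

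The second reply is that worsening would still be noticed. This largely stands. Clinician judgement alone is enough for an SSI, participants are observed in sessions, and the monitoring in Managing Study Procedure Risks runs in the right direction. That monitoring prompts contact, however. It sets no threshold and does not define an SSI. Sessions are also absent during the waitlist and between post-treatment and the three-month follow-up, so at the next assessment the scores carry more of the weight.

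Three stronger readings are tempting, and the documents do not support them:
- A reader might infer that the trial would miss people who worsen. The fault is confined to the questionnaire limb. The other routes above remain.
- A reader might infer that the more effective arm would look less safe. The protocol plans no comparison of SSIs between arms. It keeps a log.
- A reader might apply the 55.8% remission rate from Participant Numbers & Power to the 26 participants in Group 1 to count the false entries. That rate is diagnostic remission from a meta-analysis. It is not the share with a reliable fall in score, which the protocol gives no means to compute.

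**Conclusion.** The point holds for the questionnaire limb of the SSI definition. As written, the limb runs against the scoring of the symptom scales and against the Analysis Plan. Read literally, it cannot identify worsening and points to reliable improvers. This needs no assumption beyond a positive RCI and the scale directions the protocol itself gives.

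The consequence is a possible misfilling of the SSI log. Its size in participants is unknown. Sample size, power, the mixed-model efficacy analyses, the Analysis Plan's deterioration outcome and the serious-adverse-event definition and reporting are all untouched. The error is probably one of drafting, but it sits in an operative safety definition and should be corrected.

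**What to change.** Reconcile Reporting of Adverse Events with the Analysis Plan so that the questionnaire criterion for an SSI is a change of RCI size in the worsening direction of each symptom scale to which it applies. The correction should concern direction only. The safety section speaks of questionnaires in the plural, while the Analysis Plan ties the index to the OASIS. Importing the OASIS definition wholesale could drop worsening on the depression or other symptom scales, so the set of questionnaires should not be narrowed as a side effect. What follows once an SSI is identified is a clinical matter and is not part of this correction.

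If any log template or automated alert has been built from the safety section, check that it uses the corrected direction, and review any entries already made under the questionnaire limb.

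The cost is a one-sentence protocol amendment plus that check. No analysis or sample-size figure changes.
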